##### Naming of letter sounds (incl. The use of movement)

During the intervention there will be a strong focus on the coupling between letter sound and movement. To evaluate potential benefits of using movements when asked to remember letter sounds of a specific letter, a test has been constructed for the purpose. While standing, the child is asked to pronounce the letter sounds of specific letters (included letters are a, d, e, o, r, u and v which in Danish each have several possible pronunciations) which are read aloud by the assessor. The child will be told that he/she is allowed to use movements when pronouncing the letter sounds, but they are not directly encouraged to do so. For every letter sound, the child’s answer is registered as correct/incorrect/missing and whether movement/no movement was used. The results of the test are numbers of correct letter sounds pronounced in total, correct letter sounds pronounced using movements, and correct letter sounds pronounced without movements.

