### Content and organization of intervention- and control activities

#### Intervention conditions

The activities included in the two interventions vary mainly in regards to the motor modality used (i.e. hand vs. whole-body movements). In both interventions, activities have been developed with the embodied learning theory in mind, linking movement closely to the learning content. A basic element in the two interventions is the coupling of movements to letter sounds and letterforms. Children will be taught to perform a specific movement for every letter sound, and this movement-sound coupling will be used throughout the intervention. Short staccato-like letter sounds (e.g. the pronunciations of the letters “P”, “K”, “T”) are carried out as fast and powerful movements, whereas long letter sounds (e.g. the pronunciations of the letters “S”, “O”, “A”) are performed as slow and fluent movements. Moreover, when possible, the movement may be associated with objects or living creatures (e.g. the movement coupled to the sound of “S” may be associated with a snake). All movement-sound couplings are executed from left to right, i.e. the reading direction. Children in the WM group are encouraged to perform movements using their whole body and the space surrounding them. Activities in WM are mainly performed individually standing in a circle on the floor or in predefined couples/pairs. Activities in HM will be completed seated around a table and children are instructed only to use their arms and hands during the session. As for WM, activities in HM are performed individually or in predefined couples/pairs. Activities will be instructed by trained instructors and completed one at the time to ensure that all children understand and complete all tasks. Instructors will be asked to correct and support on a group level. Detailed descriptions of intervention activities are provided in Table 3.

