#### Control condition

Control activities involve learning content similar to the activities in the two intervention groups and will be conducted in parallel with the intervention activities. Teachers are told not to encourage the children to use any motor movement (e.g. hand phonemes) besides handwriting during the control sessions. Importantly, though movements are reduced to a minimal, control activities still have a strong focus on letter sounds. All tasks will be completed seated on a chair, individually or in predefined couples/pairs, using paper and pencil. Before the intervention period, tasks are printed and handed out to the teachers who will administer the control activities according to standardized procedures (Table 3). As for the two interventions, each task will be handed out and completed one at the time to ensure that all children understand and complete all tasks. Detailed descriptions of control activities are provided in Table 3.

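### The letter-sound naming test splits correct answers into raw counts with and without movement; these mainly track how often a child moved, not whether moving helped recall

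*Protocol article*

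**What the plan says.** The section on naming of letter sounds gives the purpose directly: "To evaluate potential benefits of using movements when asked to remember letter sounds of a specific letter, a test has been constructed for the purpose". The child stands, hears a letter (a, d, e, o, r, u or v) and pronounces its sounds. The child is "allowed to use movements when pronouncing the letter sounds, but they are not directly encouraged to do so". For each sound, "the child’s answer is registered as correct/incorrect/missing and whether movement/no movement was used". The results are then fixed as three counts: the total number correct, and its split into "correct letter sounds pronounced using movements, and correct letter sounds pronounced without movements".

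The arms differ in exposure to movement. Under the intervention conditions, for WM and HM: "Children will be taught to perform a specific movement for every letter sound, and this movement-sound coupling will be used throughout the intervention". In Table 3 the activity that introduces the movement-sound coupling is marked as absent from the control session. The control condition section adds: "Teachers are told not to encourage the children to use any motor movement", with handwriting the exception.

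The outcome measurements section names neither split count as primary or secondary. At most, the total score falls under the secondary outcome of general knowledge of letter-sound correspondences.

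**The concern.** The question is whether moving helps a child recall a sound. That calls for success when moving set against success when not moving, each relative to the number of tries. The listed results give only the successes. A child who moves often will have many correct answers with movement and few without, whatever movement does for recall.

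Movement use is also expected to differ by arm, because only WM and HM learn the couplings. Adjusting for baseline would not remove this, since the couplings are taught after baseline. If the split counts were read as benefit or compared between arms, the result could be reported as movement helping recall, or as intervention children knowing fewer sounds without movement, when neither is true.

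The stake is limited to this test. It is, however, the one listed test that records movement during recall, which is the mechanism the interventions are built on.

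**Working it through.** The article states no figure to reproduce. The point follows from how the results are defined; the numbers only show scale.

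**Inputs**
- Number of sounds, K: not stated. Table 2 lists a 2, d 2, e 3, o 2, r 2, u 2, v 2, so 2+2+3+2+2+2+2 = 15. Using all 15 as items is an assumption.
- Movement uptake and accuracy: not in the article; assumed, and uptake is varied.
- Group sizes for the simulation: 53 per intervention arm and 106 controls, from the sample size section.

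**Step 1: identity.** Each correct answer is given either with or without movement, so correct-with + correct-without = total correct. With the total fixed, each correct answer accompanied by a movement lowers the other count by one.

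**Step 2: equal knowledge, 10 of 15 correct in every arm.** If intervention children move on a share u of correct answers and controls on a share c, the difference in the 'without movement' count is 10 × (u − c).
- c = 0: u = 20% gives 2 sounds, 40% gives 4, 60% gives 6.
- c = 5%: 10 × (0.20 − 0.05) = 1.5, 10 × (0.40 − 0.05) = 3.5, 10 × (0.60 − 0.05) = 5.5.

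**Step 3: expected counts.** Let m be the share of sounds attempted with movement, and p1 and p0 the accuracy with and without movement. Then E[correct with] = K·m·p1 and E[correct without] = K·(1 − m)·p0. At 30% uptake and accuracy 0.60 throughout: 15 × 0.3 × 0.6 = 2.7 and 15 × 0.7 × 0.6 = 6.3. In controls at 5% uptake: 15 × 0.05 × 0.6 = 0.45 and 15 × 0.95 × 0.6 = 8.55.

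**Step 4: simulation** (500 runs, independent binomial answers, Welch t-test at two-sided 5%, control uptake 5%, accuracy 0.60 with or without movement):

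| Intervention uptake | Correct with movement (rejected) | Correct without movement (rejected) | Total correct (rejected) |
|---|---|---|---|
| 10% | 0.91 v 0.45 (90%) | 8.11 v 8.56 (28%) | 9.01 v 9.01 (6%) |
| 30% | 2.71 v 0.46 (100%) | 6.31 v 8.54 (100%) | 9.02 v 9.00 (5%) |
| 70% | 6.29 v 0.45 (100%) | 2.72 v 8.54 (100%) | 9.01 v 8.99 (6%) |

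Values are intervention v control.

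**Step 5: does the sign carry information?** At uptake 30% v 5%, let movement truly harm recall (0.50 with, 0.60 without). The with-movement count is still higher in the intervention arm, 2.25 v 0.38, rejected in 100% of runs. If movement truly helps (0.70 v 0.60), it is 3.17 v 0.53, also 100%. The sign follows uptake in both cases. Dividing by attempts within the intervention arm gives 0.50 v 0.60 under harm, 0.70 v 0.60 under benefit, and about 0.60 v 0.60 under the null, so the proportions separate the three cases.

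**Step 6: one child.** Suppose 3 of 3 sounds are right with movement and 8 of 12 without. The counts are 3 v 8 and seem to favour not moving; the success rates are 3/3 = 100% and 8/12 = 67%.

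**The case against.** The strongest reply is that the harmful analysis is not in the document. The section defines scores; it does not say that the split counts will be compared between arms. The plan for data analysis applies its models to primary and secondary outcomes, and the split counts are named as neither. A reader might infer that such a between-arm test is planned, but the text does not support that. This stands, and the point is limited accordingly. What remains is that the article itself ties these counts to the question of benefit and fixes them in a form that cannot answer it.

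A valid comparison is already present. Total correct is listed first and does not depend on movement use, and read beside it the split counts show movement use rather than harm. This also stands. Nor are attempts lost from the data, because incorrect and missing answers are registered with movement status. The gap is in the scoring, not the collection.

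A reader might also infer that movement in controls is near zero by design. That goes too far. Every child is told that moving is allowed, control teachers are only told not to encourage it, and the arms share classes. Lower use is a reasonable expectation, but its level is unknown.

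The size is assumed throughout. Even the 15 items are uncertain: the separate multiple-choice test takes 15 sounds from a, e, o, r, u and v, for which Table 2 gives only 13 (15 less the two for d).

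Finally, denominators do not give a causal answer, because the child chooses when to move.

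**Conclusion.** The point holds in a limited form. The two split counts do not serve the test's stated purpose, because they lack denominators, sum to total correct and mainly record how often a child moved. If read as benefit or compared between arms, they can show an apparent gain or deficit with equal knowledge. That deficit is 2 to 6 sounds at 20 to 60% uptake, assuming 15 items, 10 correct in every arm and no control movement. The identity behind this needs no assumption beyond equal totals; the size rests wholly on the assumed uptake and accuracy.

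The documents do not support the wider reading that the whole test is invalid or that the trial's conclusions are at risk. Total correct remains a valid randomised comparison of overall recall, although it does not isolate the effect of moving. No primary outcome or sample size depends on the split counts. The change is worth making because it is cheap and this test speaks to the proposed mechanism.

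**What to change.** 1. Use total correct as the result for the comparison between arms.
2. Report the share of answers given with movement in all three arms, as a measure of movement use. Keep the control arm, since it supplies the reference level of spontaneous movement.
3. As evidence on benefit, replace the split counts by the proportion correct among answers given with movement and among those given without. An item-level mixed model with child and letter sound as random effects would suit. Each sound is answered once per occasion, so the same child cannot be compared with and without movement on the same sound. State whether missing answers count in the denominators.
4. Label the third result descriptive, because children choose when to move.

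The cost is a change of scoring and a few lines of text; no new data are needed. The downside is that proportions will be sparse for children who rarely move, children who never move add nothing to a within-child contrast, and the result is still not causal.

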##### Letter naming fluency

A test of letter naming fluency will be included, since the speed of letter naming has been associated with e.g. word recognition and reading fluency [45, 47, 64, 76]. This Danish version of the Letter Naming test is based on the same principles as DIBELS Letter Naming Fluency [30] and has previously been used to evaluate children’s ability to name letters [65]. The test consists of a piece of paper (A4) with 12 rows of 10 letters (mixed upper- and lower case). The child is asked to name as many letters as possible in 1 min while pointing to each letter. Wrong namings are registered by the assessor. If the child does not name the letter within 3 sec, the assessor says the name of the letter and encourages the child to name the next letter. If all 10 letters in the first row are named incorrectly, the test is discontinued. One row of 10 letters will be provided as practice. Result from the test is numbers of letters named correctly.

##### Working memory

To our knowledge, there are no previous studies on pre reading, motor-enriched learning and working memory. Therefore, we include 1-back task as a visual working memory task and a digit span task as an auditory working memory task. Through these two working memory tasks, we can investigate covariation of unspecific working memory and the primary outcome measures of this study. Covariation of academic performance (in math) and working memory in longitudinal classroom-based interventions has previously been reported [5].
**1-back task** To assess working memory a 1-back task will be completed by each child. A 1-back task was chosen, since a recent study including seven-year-old children reported a mean accuracy score between 60 and 70% in a comparable 1-back task, whereas the accuracy score in the included 2-back task was between 30 and 40% [63]. This 1-back task is constructed of representations of symbols (car, cloud, globe, note, headphones, airplane, plate, key, eye and bicycle); one symbol is presented at the time. On the 1-back task, children have to compare the symbol seen on the screen with the symbol previously presented. Children are instructed to press “yes” (a green key) on the keyboard if these two symbols are identical and “no” (a red key) if they are dissimilar, as fast and as accurate as possible. The test consists of 20 practice trials (30% “yes” trials) followed by two test blocks of 20 trials each (30% “yes” trials). Symbols are presented for 500 ms followed by a 3000 ms blank screen. The response window and inter-stimuli interval is 3500 ms each. The results from the test constitute number of correct and wrong “yes” and “no” answers, mean reaction time for correct “yes” and “no” answers, and number of non-responses in the two test blocks. Normative data on the n-back task for children and young adolescents have previously been reported [63].**Digit span** The digit span task is a subtest of the Wechsler Intelligence Scale for Children – fourth edition (WISC-IV) [88] and is used to assess auditory working memory, attention, and concentration. The test consists of two subtests; digit span forward and digit span backwards. In each subtest, participants hear a sequence of numerical digits after which they are asked to recall the digit sequence in the same order (subtest 1) or in reverse order (subtest 2). The sequences are said by the administer with a speed of one digit per second, starting with a sequence of two digits, then three digits, then four digits etc. Within each sequence length, two trials are provided. If the answer is incorrect on both these trials, the test is discontinued. The results from the tests constitute the number of correctly remembered sequences and the number of digits in the longest correctly remembered sequence.

##### Fine motor skills (9-hole pegboard)

The 9-hole pegboard test is a standardized test which has previously been used in children to evaluate fine motor skills [50, 75]. The 9-hole test consists of a square board with nine 1.3 cm (0.5 in.) deep holes which are spaced 3.2 cm (1.25 in.) apart. Sitting on a chair with the board placed in from of them, children are instructed to pick up the pegs one at a time, using the dominant hand only and put then into the holes in any order until the holes are all filled. Then the participant removes the pegs one at a time and return them to the container. The participant gets one practice trial before timing the test with a stop watch, starting when the child touches the first peg. The test is conducted with dominant hand and non-dominant hand. The test is conducted with the dominant hand first.

#### Motivation

A modified version of Intrinsic Motivation Inventory (IMI) [54] will be used to measure intrinsic motivation for the PLAYMORE activities. The original items of the IMI are translated into Danish using a translation-backtranslation process [77]. The inventory is reduced to six questions related to intrinsic motivation (question 1–3) and feeling of competences (question 4–6). Because the inventory will be used in children, the original 7-point likert scale is converted to a 4-point likert scale (1, not true at all, 2, only slightly true, 3, almost true; 4, true). Immediately after one session in week two, four, six and eight, an assessor will read the questions aloud for the children one by one. This inventory measures participants’ subjective experience related to an activity in an experiment and has previously been used in other studies on the motivational effect of integrating physical and learning activities in primary schools [86]. Means from question 1–3 and from question 4–6 will be calculated for each child and used as measures for intrinsic motivation and feeling of competences, respectively.

#### Compliance to the intervention

Teachers/instructors will be asked to keep a written log of attendance of each child. Specifically, data on 1) presence (yes/no), and 2) active participation (yes/no) will be registered. Moreover, teachers/instructors will note whether each session has been completed (yes/no) and to what degree it followed the protocol (scale 1–5).

### Plan for data analysis

In accordance with the Consolidated Standards of Reporting Trials (CONSORT) 2010 for randomized controlled trials [57], flow of participants will be reported. Descriptive statistics will be summarized across schools and classes for each group. Potential differences at baseline between subjects included and excluded in the analyses (e.g. drop-outs) as well as differences between groups at baseline will be tested. Further, compliance to the intervention will be summarized for each group. Intention-to-treat analyses will be performed to assess the effect of the intervention on primary as well as secondary outcomes. Multilevel mixed model will be used as this model is able to provide an unbiased estimate given missing data assuming data is missing at random conditional on variables included in the model [83]. Patterns of missing data will be investigated. To account for the cluster structure in the data (i.e. subjects within classes within schools), class and school will be included as random effects in the model. Due to the randomized design, which is used to ensure equal distribution of confounding variables between groups, we will only adjust for potential confounding variables (e.g. sex, age) which show unevenly distribution between groups at baseline. In addition, per protocol analyses will be conducted using above-mentioned approach including participants with a participation rate above 90%. In addition, structural equation models (SEMs) will be used for mediation analyses to explore potential mediators.

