### Study design

The study will be conducted as a three-armed randomized controlled trial including two intervention groups and one control group (CG) (Fig. 1, study design and flow of participants). Intervention activities will be completed as either whole-body movements (WM, intervention group I) or hand movements (HM, intervention group II) over an 8-week period at four primary schools. Using random selection of sealed envelopes, participants will be randomized stratified by class in an approximate 1:1:2 fashion to either WM, HM or CG. Specifically, within each class six subjects will be assigned to WM, six subjects to HM, while the remaining subjects will constitute the CG. The project leader will be responsible for all steps related to the enrollment and allocation of participants. Outcome measurements will be collected before and after the intervention period enabling assessment of the intervention effects. A schematic diagram of time schedule of enrolment, interventions and assessments are presented in Table 1.

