**Fig. 1 Fig1:**
[figure not shown]
Study design and flow of participants

**Table 1 Tab1:** Schedule of enrolment, interventions and assessments in the PLAYMORE study

		STUDY PERIOD											
Activity or assessment	School/class /group /individual level	Recruite-ment	Baseline	Intervention period (8 weeks)								Post	3-month follow-up
				1	2	3	4	5	6	7	8		
Contact to schools	School	**●**											
Eligibility screen	Individual	**●**											
Consent (parents)	Individual	**●**											
Inclusion	Individual	**●**											
Randomization	Individual		**●**										
**INTERVENTIONS/CONTROL** (3*30 minutes/week)													
Whole-body movements	Group (6 subjects)			**●●●**	**●●●**	**●●●**	**●●●**	**●●●**	**●●●**	**●●●**	**●●●**		
Part-body movements	Group (6 subjects)			**●●●**	**●●●**	**●●●**	**●●●**	**●●●**	**●●●**	**●●●**	**●●●**		
Control	Group (app. 12 subjects)			**●●●**	**●●●**	**●●●**	**●●●**	**●●●**	**●●●**	**●●●**	**●●●**		

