### Structure and learning content of the activities

During the 8-week intervention period, three sessions of approximately 30 min duration will be completed each week, counting 24 sessions in total. At the schools, trained instructors will administer activities in the two intervention groups, while the usual schoolteachers will administer the control activities. Activities focus on the acquisition of letterforms, letter-sound correspondences and reading and spelling of short words. The learning content of the activities is identical in the three groups and vary mainly in regard to the degree of bodily movement. Activities are developed based on the research-founded Danish teaching material, *Fandango Mini*, which is recognized and used by several preschool teachers in Denmark [38]. The material is based on a synthetic phonics approach and is scheduled as a 20-week systematic course covering both standard and conditional pronunciations of the letters. From the very beginning, students practice reading and spelling of words composed of the letter-sounds trained so far.

The first six weeks follow the same weekly structure involving the same type of activities. During each of these six weeks, four to five new letters and related sounds and two to four new words containing these letters and sounds (*target words*) will be studied intensively (Table 2). Additional words not classified as target words will be presented to the children during the intervention period, but focus will be on studying the target words. The last two weeks, activities link what has been learned during the first six weeks and involve activities focusing on word reading and the composition of minor sentences containing the words trained. Thereby, the children will be taught 25 letters and the related sounds (standard and conditional pronunciations) and 18 target words during the intervention period. An example of a protocol for one week (week 1–6) and detailed description of intervention−/control activities are provided in Table 3. Components specific for each intervention- or control condition are described in the sections below.

**Table 2 Tab2:** Letters, letter sounds, and target words trained during each week of the intervention period

Week	1							2					3					4					5					6						7 and 8
**Letters**	l	å	s	m	e			b	i	u		y	n	k	f	a		æ	h	t	d		g	p	o		j	ø	r		c	v		all

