The PLAYMORE study is unique as the methodology is stringent including theoretically founded activities that are well-described. Another strength of the study is the blinding of assessors at baseline and 8-weeks follow-up, thereby limiting the risk of bias. In addition, participants will be blinded at baseline, however, due to the nature of the study, it will not be possible to blind participants during the intervention period or at follow-up, which could introduce bias. However, with the age of the participants in mind, we do not expect this to influence the results significantly. The study includes a highly relevant control group completing the exact same academic content as the intervention groups, enabling a fair comparison between the groups. However, we are aware of the limitations within the control group and that these limitations may introduce bias. Usual teachers will administer the control activities while trained instructors will instruct the intervention activities, which may cause differences (e.g. comfort, newsworthiness) between the groups not associated with the differences in bodily movement. This decision is made for practical and ethical reasons, since it enables children without written consent to participate in the control activities along with their peers. In addition, the children-to-teacher rate is approximately twice as large in the control group compared to the intervention groups, which may affect the group dynamics. However, since teachers/instructors are asked to correct and support on a group level, the differences in children-to-teacher rate will most likely not affect the time spend correcting/supporting each child.

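### The planned mixed model has random effects for class and school but none for the teaching group within class, so standard errors of the arm contrasts are too small if children taught together have correlated outcomes

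*Protocol article*

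**What the plan says.** Children are randomised individually, stratified by class. Under Study design, "within each class six subjects will be assigned to WM, six subjects to HM, while the remaining subjects will constitute the CG". Table 1 gives the delivery unit as a group of six in each intervention arm and a group of about twelve in the control arm. Under Structure and learning content of the activities there are 24 sessions of about 30 minutes, and "trained instructors will administer activities in the two intervention groups, while the usual schoolteachers will administer the control activities". Under Intervention conditions, "Instructors will be asked to correct and support on a group level". The Discussion says that the children-to-teacher ratio is about twice as large in the control group, "which may affect the group dynamics".

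The Plan for data analysis describes the cluster structure as "subjects within classes within schools" and says that "class and school will be included as random effects in the model". The article mentions no term for teaching group, instructor or class-by-arm, and no robust variance at that level. This is not a detail left open for a later plan: the article names the levels of clustering and omits the one at which teaching is delivered.

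**The concern.** Children who are taught together share peers, pair work, session conduct and group-level feedback, so their post-intervention scores may be more alike than those of classmates taught in another arm's group. Random allocation makes the groups comparable at the start but does not keep outcomes independent once teaching begins.

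The class intercept does not deal with this. It is common to the WM, HM and CG children of a class, so it cancels from a within-class contrast (exactly when arm proportions are equal across classes, nearly so otherwise). School is constant within class and cancels too. Variation between the three groups of a class is then treated as independent child-level noise, which understates the standard errors. The contrasts affected are those the trial was set up to test: each intervention against control, and the two interventions against each other, on both primary outcomes. Ordinary group-to-group variation could be declared a movement effect more often than the nominal 5%.

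**Working it through.** **The plan's own figure.** A one-way ANOVA with three equal groups, effect size f = 0.25 and alpha 5% has noncentrality 158 × 0.25² = 9.875 at N = 158, and power 0.802. Then 53 + 53 + 106 = 212, and 212/0.8 = 265. All three stated figures reproduce. The calculation treats children as independent.

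**Inputs.** From the article: groups of 6/6/about 12 per class, 265 enrolled, 20% loss. Assumed: 265/24 ≈ 11 classes. Analysed group sizes after loss are 6 × 0.8 = 4.8 and 12 × 0.8 = 9.6. The group ICC ρ is not in the article, so a range including zero is used.

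**Formula.** Set the within-class variance to 1, of which ρ lies between teaching groups. Over K classes with group sizes m₁ and m₂:

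- true variance of an arm contrast = [2ρ + (1 − ρ)(1/m₁ + 1/m₂)]/K
- variance without a group effect = (1/m₁ + 1/m₂)/K

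K cancels from the ratio.

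**WM (or HM) vs CG.** 1/4.8 + 1/9.6 = 0.3125, so the ratio is (2ρ + 0.3125(1 − ρ))/0.3125 = 1 + 5.4ρ.

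- ρ = 0.02: ratio 1.108; SE √1.108 = 1.053 times the modelled one
- ρ = 0.05: ratio 1.27; SE 1.127 times
- ρ = 0.10: ratio 1.54; SE 1.241 times

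**WM vs HM.** 1/4.8 + 1/4.8 = 0.4167, so the ratio is 1 + 3.8ρ: 1.076, 1.19 and 1.38.

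The two-sided type I error of a nominal 5% test is 2[1 − Φ(1.96/√ratio)].

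**Simulation.** Two kinds of check with no true effect, 11 classes each: a class-effect analysis without a class-by-arm term (4,000 runs), and a REML fit with a random class intercept and Wald test (5 WM, 5 HM, 7 to 13 CG per class, class ICC 0.10 assumed, 3,000 runs).

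| Contrast | Group ICC | Formula | Class effect, 5/5/10 | Class effect, 6/6/12 | Random class intercept |
|---|---|---|---|---|---|
| WM vs CG | 0 | 5.0% | not run | 5.4% | 5.3% |
| WM vs CG | 0.02 | 6.3% | 5.9% | 6.5% | 6.7% |
| WM vs CG | 0.05 | 8.2% | 9.3% | 8.9% | 10.1% |
| WM vs CG | 0.10 | 11.4% | 12.2% | 14.4% | 11.7% |
| WM vs HM | 0 | 5.0% | not run | not run | 4.9% |
| WM vs HM | 0.02 | 5.9% | not run | 6.3% | 5.9% |
| WM vs HM | 0.05 | 7.2% | not run | 8.3% | 7.2% |
| WM vs HM | 0.10 | 9.5% | not run | 11.9% | 9.4% |

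HM vs CG behaves as WM vs CG, because the two intervention groups have the same size. The inflation grows with group size (for 6/6/12 the WM vs CG ratio is 1 + 7ρ), which explains part of the spread. A paired analysis of class-by-arm means, which uses the teaching group as the error unit, stayed between 4.4% and 5.7% in all simulations.

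**The case against.** The strongest reply is that the size rests on a number the article does not supply. At ICC 0 the planned standard errors are correct; at 0.01 the simulated error is 5.5%. There are reasons to expect a small ICC: groups are formed at random within class, contact is about 12 hours (24 × 30 minutes), the content is scripted and the same in all arms, and instructors and teachers are trained. This stands as a limit on size, and nothing in the article supports 0.10 in particular. It does not justify the omission, because the error runs in one direction and the Discussion itself raises group dynamics.

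A reader might also infer several stronger points that the article does not support:

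- **One instructor per group.** The number of instructors, and whether one covers several groups or both intervention arms, is not stated. If instructors span groups, there is a further, crossed correlation that a class-by-arm term does not capture.
- **A missing child-level term.** The article does not say that scores from several occasions enter one model. If they did, omitting the term would make standard errors of change contrasts too large, the opposite direction.
- **Only four schools for a school variance.** School cancels from within-class contrasts, so this hardly touches them.
- **Bias from uneven class sizes.** With 11 classes of 20 to 28 children and class effects perfectly correlated with class size, the bias in WM vs CG was at most 0.02 SD, about 0.13 SE. That is no reason to switch to fixed class effects.

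**Conclusion.** The point holds as a conditional statement about precision. The planned random effects omit the teaching group, and the standard errors of all three arm contrasts are too small whenever the teaching-group ICC is positive. With about 11 classes, type I error for WM vs CG is about 5% at ICC 0, 6 to 7% at 0.02, 8 to 10% at 0.05 and 11 to 14% at 0.10. For WM vs HM it is about 5%, 6%, 7 to 8% and 9 to 12%. The direction is firm. The size rests on the assumed ICC and on a class count inferred from 265/24; children without consent also attend the control sessions, so analysed group sizes may differ.

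It would be too strong to say that the confidence intervals and p-values are wrong outright, because that requires a positive ICC. It would also be wrong to read the missing term as the source of the instructor-versus-teacher and group-size differences between arms. Those are systematic, the Discussion already discloses them, and no random effect removes them. The severity is should-fix.

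**What to change.** In the Plan for data analysis, keep the class and school terms and add a random class-by-arm (teaching-group) effect. Use Kenward-Roger or Satterthwaite degrees of freedom, since there are only about 11 groups per arm, and report the estimated group ICC with the primary results. Where one instructor teaches several groups, also consider an instructor effect.

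Class and arm identify the teaching group for every child, so no new data are needed. The cost is wider intervals for arm vs control (SE about 5% larger at ICC 0.02 and about 24% at 0.10) and fewer degrees of freedom: with 11 classes and three arms, about (11 − 1) × (3 − 1) = 20 for the class-by-arm stratum. Because the sample size of 212 analysed children assumes independence, power should be re-examined over the same ICC range.
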